### Study flow

In the beginning, the patient receives written information and an oral explanation of the study from the physician and is asked to give written informed consent. Patients have the right to withdraw from the study at any point if they so wish with no consequences to their treatment.

The patients are asked to give their consent to participate in the study via the Suomi.fi-service, an electronic service requiring strong identification. The research assistant signs the consenting patients in the Helsinki University Hospital Electronic Case Report Form (HUSeCRF) system which randomizes the patients. The patients then fill in the baseline information forms online in the HUSeCRF system. The research assistant has access to the interim results. In case the research assistant reports significant differences in outcomes between intervention and control groups midway through the study, the study will be terminated earlier than planned.

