### Follow-up

The follow up is primarily performed with the HUSeCRF system. The patient receives reminders by text messages and emails when it is time to fill in the 3, 6 and 12 month follow up surveys. If a patient has not filled in the questionnaires after three reminders, the study nurse contacts him or her by telephone to collect the outcome data.

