### Statistical analysis

A research assistant will store the baseline data in pseudonymized format into the HUSeCRF database. Access to the database is given to those members of the research group who analyze the data. Access to HUSeCRF is with personal codes and includes phone verification.

The codes that link patient information and study numbers are saved in the Key register, which can only be accessed by the PI and the study coordinators.

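### The research assistant who registers patients for randomisation can also see comparative interim results and reports the differences that end the trial, while enrolment is still open

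*Protocol article*

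**What the plan says.** The protocol article, Study flow, gives one role three tasks.

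- Registration: "The research assistant signs the consenting patients in the Helsinki University Hospital Electronic Case Report Form (HUSeCRF) system which randomizes the patients".
- Access: "The research assistant has access to the interim results".
- Reporting: "In case the research assistant reports significant differences in outcomes between intervention and control groups midway through the study, the study will be terminated earlier". No recipient of the report is named.

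Other tasks lie elsewhere. Under Study flow, "the patient receives written information and an oral explanation of the study from the physician and is asked to give written informed consent", and consent is recorded electronically: "The patients are asked to give their consent to participate in the study via the Suomi.fi-service". Under Follow-up, "The follow up is primarily performed with the HUSeCRF system", with automatic reminders; if three of these bring no reply, "the study nurse contacts him or her by telephone to collect the outcome data".

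The Statistical analysis section names a separate group with data access: "Access to the database is given to those members of the research group who analyze the data". It also says that a research assistant stores the baseline data, without saying whether this is the same person.

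**The concern.** Running comparative results are normally kept from people who have a hand in conducting a trial, because knowing them can change conduct without anyone intending it. That protection matters more here than in a blinded trial with objective endpoints. The Discussion says that efficacy rests only on subjective patient-reported measures. The control group receives usual care alone for six months, so patients know whether they have an online programme. No blinding is described. Restricting knowledge of the interim comparison is one of the few safeguards left, and Study flow gives it up by an explicit statement.

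Two things are at stake. Results known to the assistant could reach the physician who explains the trial to new patients, or the nurse who telephones non-responders. And the person who holds the results also decides when and what to report, on which the length of the trial depends. The Discussion adds a further results-dependent step: recruitment may continue, to 120 per arm in a subgroup, if effects differ between subgroups.

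**Working it through.** The point concerns who holds which role, so most of the check is a comparison of sections. The arithmetic only describes the calendar.

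**1. Does the assistant see outcomes by arm?** Study flow has the assistant report differences between intervention and control groups. Nobody can report such differences from completion status or pooled data. The access must therefore be to comparative results.

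**2. Is enrolment open at that time?** Study duration and timeline puts enrolment in months 1 to 24 and follow-up in months 3 to 36. The two overlap for about 24 − 3 = 21 months.

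**3. Who does what?**

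| Task | Role | Interim access stated? |
|---|---|---|
| Explain the trial, ask for consent | Physician | No |
| Enter the patient in the system after consent | Research assistant | Yes |
| Allocate | HUSeCRF system | Not applicable |
| Send reminders | Text messages and emails | Not applicable |
| Telephone non-responders | Study nurse | No |
| Report differences that lead to termination | Research assistant | Yes |

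The overlap of registration, interim access and reporting in one role is stated in the text. The assistant's registration step comes after consent, and the system allocates, so knowing the results gives no stated means of steering allocation or altering a patient's answers.

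**4. How many patients are registered while results could exist?** Assume uniform recruitment, which the article does not state: 360 / 24 = 15 per month, or 5 per arm per month.

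- After the first three-month forms can exist (month 3): 21 × 15 = 315.
- After the first six-month forms, the primary time point, can exist (month 6): 18 × 15 = 270.

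These figures overstate the time during which a difference could be read. At month 6 only 3 × 15 = 45 patients, 15 per arm, would have reached three months.

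The one timing the article gives is midway, which it does not define. Two readings, before any losses:

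- Middle of enrolment (month 12): (12 − 6) × 15 = 90 patients have reached six months, 30 per arm, and 12 × 15 = 180 are still to be enrolled.
- Middle of the 36-month timeline (month 18): (18 − 6) × 15 = 180 have reached six months, 60 per arm, and 6 × 15 = 90 are still to be enrolled.

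Under either reading, a quarter to a half of the 360 would be registered after the midway look by someone who has seen it. None of these counts measures bias.

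**The case against.** The strongest reply is that the tasks through which bias would act belong to other people. The physician presents the trial, reminders and then the nurse pursue missing forms, patients complete their own outcomes, and the system allocates. No section says that the physician or the nurse sees interim results. Harm through them needs a leak that the article does not describe. This stands, and it limits the point to an indirect route.

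A reader might infer that recruitment and follow-up are run by someone who knows which arm is ahead. The documents do not support that: Study flow and Follow-up give those tasks to others. Nor should the 315 and 270 be read as patients exposed to a visible difference; they follow from the calendar and an assumed rate.

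It can also be said that a condensed article leaves detailed user rights to the full protocol. That would answer a complaint about silence. Here the article positively grants the access and assigns the reporting, so the matter is a stated choice. If the access is narrower in practice, the text should say so.

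Finally, the use of an undefined significant difference as the trigger for stopping may be the weightier problem in the same paragraph. It is a separate one. A well-specified boundary would still leave the registering role looking at outcomes by arm.

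**Conclusion.** The point holds in a limited form. One role registers patients for randomisation, sees comparative interim results and reports the differences that end the trial, and does so while enrolment is open. Interim data are therefore not kept from trial-conduct staff. The possible routes to harm are results passing from the assistant to the physician or the nurse, and the assistant's discretion over when and what to report.

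The size of any bias cannot be derived from the documents. On an assumed uniform 15 patients per month, 90 to 180 of 360 would be registered after a midway look, depending on what midway means. The conclusion itself does not depend on that rate. It rests on the reading that interim results means results by arm, which the reporting task requires, and on the Study flow wording that the same role registers patients. The weakness is real and cheap to correct, and it should be corrected. It is no evidence that allocation or outcome data are compromised.

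**What to change.** In Study flow, replace the sentence on interim access with three provisions.

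1. The research assistant's HUSeCRF rights cover sign-in, baseline entry and form-completion status, without outcome values by arm.
2. The interim comparison is run only at the planned midway point, by a named role within the analysing group that already has database access under Statistical analysis. That person does not enrol or contact patients. The condition must be written down, because the article does not say that analysing members have no patient contact.
3. Recruiting and follow-up staff are told only whether the trial continues or stops.

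The cost is a change of user rights, a few lines of protocol text, and the designation of an analysing member without patient contact. The assistant can then no longer see or report results. Whether the rights can be set this finely in HUSeCRF is not stated and should be checked. As the trial was still running when the article was written, the amendment should also state what access the assistant has had up to that date.

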### Outcome assessment

The primary outcomes in the study are self-reported functional ability and quality of life as measured on a scale from 0 to 10 and functional ability measured by the WHO Disability Assessment Schedule (WHODAS) instrument at six months. All outcomes of the study are presented in Table 1.

**Table 1 pone.0316169.t001:** Outcomes of the RCT and the timepoints of measurement.

	Baseline, 0 months	3 months	6 months	12 months

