### Analysis plan

All randomized participants will be analyzed in accordance with the intention-to-treat principles. Baseline data will be summarized as counts and percentages for categorical variables and mean values with standard deviation (SD) or median values with interquartile ranges (IQRs) for normally distributed or skewed continuous variables, respectively. Changes in primary and secondary outcomes over time and differences between intervention groups will be examined using generalized linear mixed models with time (0, 3, 6 and 12 months), intervention group, and interaction between group and time as fixed effects, and participants as a random effect. The most suitable correlation structure will be determined from the data based on multiple measures, including Akaike’s and Bayesian Information Criteria. Causal Directed Acyclic Graphs will be used in order to select a minimal adjustment set of fixed effect variables for mixed modeling on repeated measures. Benjamini–Hochberg procedure will be applied to correct for multiple testing. The statistical analyses will be carried out using R statistical computing environment [58].

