### Power calculations

It is hypothesized that the AIR program is equal in effect to the e-therapy. Additionally, it is hypothesized that both the AIR program and the e-therapy are more effective than TAU. According to simulations carried out based on a previous report [25] it was estimated that a sample size of at least 90 individuals per experimental group is required for reaching statistical power of >80% for outcome measures demonstrating improvement in AIR patients as compared to treatment equivalent to relaxation therapy (RT). This sample size was sufficient for all 9 out of 9 previously studied outcome measures reflecting functional impact, clinical severity, pain catastrophizing, severity of anxiety and depressive symptoms, perceived health status, psychological inflexibility, and mindfulness at post-treatment and three-month follow up. To overcome loss to follow up, we aim at 120 patients per each treatment arm. Please see details on the power analyses in S2 Appendix.

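### The rule that ends the whole trial on a significant midway difference has no named outcome, timing or adjusted threshold, and the analysis plan does not account for the look

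*Protocol article*

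**What the plan says.** The rule is in the protocol article, Methods, Study flow. "The research assistant has access to the interim results", and if that person reports "significant differences in outcomes between intervention and control groups midway through the study, the study will be terminated earlier than planned". The same section gives this role a part in enrolment: "The research assistant signs the consenting patients in the Helsinki University Hospital Electronic Case Report Form (HUSeCRF) system which randomizes the patients".

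The rest of the article bears on the rule as follows:

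- **Outcomes.** Outcome assessment names three primary outcomes at six months. It begins "The primary outcomes in the study are self-reported functional ability and quality of life as measured on a scale from 0 to 10" and adds WHODAS.
- **Hypotheses.** Power calculations opens with "It is hypothesized that the AIR program is equal in effect to the e-therapy", and adds that "both the AIR program and the e-therapy are more effective than TAU". There are therefore two superiority contrasts against TAU and one comparison between the active arms.
- **Multiplicity.** The Analysis plan says only that "Benjamini–Hochberg procedure will be applied to correct for multiple testing". It does not mention repeated looks.
- **Sample size.** Power calculations gives at least 90 per group for power above 80%, raised to 120 per arm for loss to follow-up. It mentions no interim analysis.

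**The concern.** The article states who triggers the stop, on what ground, and with what consequence. It does not say how the error rate is controlled. A test that can reject midway and again at the end has two chances of a false positive. If each chance is taken at the usual level, the overall rate exceeds that level.

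Three further consequences follow.

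- A trial stopped because an estimate was large enough to be significant reports, on average, too large an effect.
- The trigger is a difference between intervention and control, but the consequence falls on the whole study. A TAU contrast could therefore end data collection for AIR versus iCBTpss, the first-listed hypothesis.
- The role that sees interim results also signs patients into the randomising system, in a trial whose outcomes are self-reported.

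**Working it through.** **Inputs from the article.** Three primary outcomes; two contrasts against TAU; 90 evaluable and 120 randomised per arm (3 × 120 = 360); enrolment over months 1-24.

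**Inputs assumed.** Two-sided alpha 0.05 at each look; information fraction t = 0.5 at the look, with a range of 0.25-0.75; correlation between outcomes 0.5-0.7; equal arms sharing one TAU group.

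**The plan's own figure.** The 90 per group cannot be reproduced. It comes from simulations detailed in S2 Appendix, and the article gives no effect size, SD or alpha. With alpha 0.05 and power 80% assumed, it back-solves to d = (1.960 + 0.842) × √(2/90) = 0.418 SD. Also 90/0.75 = 120, so the inflation corresponds to 25% loss.

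**1. One test, two looks.** Under the null the two z statistics are bivariate normal with correlation √t. The error rate is 1 − P(|Z1| < 1.96 and |Z2| < 1.96).

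| Information at the look | Type I error |
|---|---|
| 0.25 | 9.1% |
| 0.50 | 8.3% |
| 0.75 | 7.3% |

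**2. Three outcomes × two TAU contrasts, t = 0.5.** Simulated chance of at least one false rejection:

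| Procedure | Correlation 0.5 | Correlation 0.7 |
|---|---|---|
| Benjamini-Hochberg, final look only | about 4.5% | about 4.2% |
| Benjamini-Hochberg at both looks | about 7.8% | about 7.2% |
| Any uncorrected p < 0.05 at the interim, Benjamini-Hochberg at the end | about 23% | about 21% |

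**3. Exaggeration at a stop.** With SE = √(2/n) and μ = d/SE, the mean estimate given z > 1.96 is SE × [μ + φ(1.96 − μ)/Φ(μ − 1.96)], where φ and Φ are the standard normal density and distribution function. For d = 0.30 and n = 45, SE = 0.211 and μ = 1.423, so the mean estimate is 0.546 and the ratio to the truth is 1.82.

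| True d | n per arm | Mean estimate at a stop | Ratio to truth |
|---|---|---|---|
| 0.30 | 45 | 0.55 | 1.8 |
| 0.30 | 60 | 0.48 | 1.6 |
| 0.418 | 45 | 0.58 | 1.4 |
| 0.418 | 60 | 0.53 | 1.3 |

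**4. AIR versus iCBTpss.** The 95% CI half-width in SD units is 1.96 × √(2/n). It is 0.29 at n = 90 and 0.41 at n = 45. How far a stop would move it depends on what "midway through the study" means. With uniform accrual, 360/24 = 15 patients enter per month:

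- Month 12: 15 × 12 = 180 enrolled, of whom 15 × 6 = 90 have reached six months (90/360 = 0.25 of the information).
- Month 18: 15 × 18 = 270 enrolled, of whom 15 × 12 = 180 have reached six months (180/360 = 0.50).

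Suppose the stop comes at month 18. If follow-up also ends, about 45 per arm are evaluable (60 × 0.75) and the half-width is 0.41. If all 270 are followed up, about 67.5 per arm are evaluable (90 × 0.75) and the half-width is 1.96 × √(2/67.5) = 0.34.

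**5. A bound that works for one test.** O'Brien-Fleming limits at t = 0.5, |z| ≥ 2.80 at the interim and 1.98 at the end (two-sided p of 0.0052 and 0.0480), give an overall error of 0.050.

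**The case against.** The strongest reply is that a boundary is the kind of detail a journal article leaves to the full protocol or the analysis plan. The article cites an ethics-approved protocol that is not shown, so a proper threshold may exist there. That stands as a caution: every error rate above is conditional on an unadjusted 0.05. It does not remove the point, because the article does not merely stay silent. It prints a mandatory rule, and nothing in its analysis or sample-size sections allows for it.

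Some stronger readings are tempting, but the text does not support them.

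- **Any single outcome at p < 0.05 stops the trial.** A reader might infer this from the plural outcomes and the bare word significant. The text neither says nor excludes it. Since the Analysis plan does name Benjamini-Hochberg, the 21-23% figure is a worst case and not the headline.
- **AIR versus iCBTpss would end at half size.** That needs both a particular meaning of midway and the end of follow-up, and neither is stated.
- **AIR versus iCBTpss needs the full sample.** Power calculations sizes AIR against a relaxation-type treatment. It gives no margin or power for AIR versus iCBTpss.
- **Interim knowledge biases enrolment.** Physicians inform patients, consent is electronic, the system allocates, patients complete their forms online, and the study nurse telephones non-responders. The overlap of roles is poor practice, but the article shows no concrete route to bias.
- **The 12-month results against TAU would be lost.** Controls are offered either programme after six months, so those contrasts are already diluted.

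**Conclusion.** The point holds. As printed, the rule obliges the whole three-arm study to stop on an undefined significant difference, and the planned analysis takes no account of the look.

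If nominal two-sided 0.05 is used, one test carries about 8.3% error at half the information, and the inflation persists from 25% to 75% information. Applying the named multiplicity procedure at both looks does not remove it: about 7-8%, against 4-5% for one look. The worst case of 21-23% requires an uncorrected interim trigger on any outcome. The multiplicity figures assume outcome correlations of 0.5-0.7.

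Estimates at a stop would be about 1.3 to 1.8 times the truth for a true d of 0.42 down to 0.30 with 45-60 per arm. The loss of precision for AIR versus iCBTpss is real, but its size is open: a half-width of up to 0.41 SD at 45 per arm, against 0.29 SD at 90.

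**What to change.** Delete the efficacy stop from Study flow. Remove by-arm outcome access from the role that signs patients into the randomising system until the 6-month primary data are complete.

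If the sponsor wants to keep a look, replace the sentence with a rule that fixes the following:

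- one look, at 50% of the 6-month primary data;
- the primary outcomes and contrasts it covers;
- an O'Brien-Fleming-type bound: |z| ≥ 2.80 at the interim and 1.98 at the end for a single test, or the corresponding levels (0.0052 and 0.0480) carried through the multiplicity procedure. The 0.050 check above covers a single test, so the combined procedure should be simulated before it is adopted;
- a statistician not involved in enrolment to run it;
- what happens to enrolled patients' follow-up and to AIR versus iCBTpss after a stop. Continuing those two arms alone would need a new allocation scheme, which is more than a change of wording.

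Deletion costs one sentence, a change of access rights in the eCRF, and a written amendment, for which the article already provides. The trial gives up the chance to stop early on a nominal p < 0.05.

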### Follow-up

The follow up is primarily performed with the HUSeCRF system. The patient receives reminders by text messages and emails when it is time to fill in the 3, 6 and 12 month follow up surveys. If a patient has not filled in the questionnaires after three reminders, the study nurse contacts him or her by telephone to collect the outcome data.

### Study duration and timeline

The study will have an overall duration of approximately 30 months and will be considered completed at the latest 12 months after the recruitment target is achieved.

The study timeline is the following:

Months 1–24: Selection and enrolment (starting from 1.1.2022) of the patients and database implementation.

Months 3–36: Follow-up (3, 6, and 12 months) and database implementation.

Months 24–36: Analysis of data and final dissemination of results.

### Participants and recruitment

#### Inclusion criteria

Age 18 to 65 yearsPersistent somatic symptoms, fibromyalgia, chronic fatigue syndrome, and post COVID-19 as predefined subgroups (please see S1 Appendix. Diagnostic criteria).

Diagnostic examinations have ruled out the potential somatic or psychiatric reasons for the symptoms ANDDisabling symptoms have lasted at least 3 months ANDPatient is willing to receive an online, mostly self-management intervention.

#### Exclusion criteria

Patients for whom participation could be overly demanding because of physical constraints (for example, patients who cannot write because of dystonia or bedridden patients)Patients with presence of severe psychiatric and severe somatic disorders (e.g. moderate or severe depression or newly onset cancer) for whom the study could be overly strenuous.Patient has received either or both of the investigated interventions previously

### Interventions

#### Amygdala and insula retraining program (AIR)

The amygdala and insula retraining program (AIR) consists of novel brain retraining approaches focused on hypothetically interrupting and retraining the conditioned defensive hyper-stimulation of the sympathetic nervous system and aspects of the immune system by the amygdala and insula, to bring the brain and body back to homeostasis [23]. It includes supportive techniques such as breathing, meditation, and neurolinguistic programming. The patients are invited to an online program of video session and eight weekly two hour webinar sessions followed by three monthly webinar sessions. The patients are assigned to do daily homework that takes approximately 15 to 20 minutes to complete. The provider of the program monitors the participation of the patients in the program. The patient needs to have an e-mail address, an electronic device (smartphone, tablet or computer) and means for electronic identification to receive the intervention. The AIR program is offered to patients of the outpatient policlinics only as a part of this randomized controlled trial.

In addition to the study intervention, patients receive treatment as usual (TAU).

